## Abstract

Mobile health (mHealth) could be widely used in the population to improve access to psychological treatment. In this paper, we describe the development of a mHealth intervention on the basis of supportive self-monitoring and describe the protocol for a randomized controlled trial to evaluate its effectiveness among smartphone users with psychological distress. Based on power analysis, a representative quota sample of *N* = 186 smartphone users will be recruited, with an over-sampling of persons with moderate to high distress. Over a 4-week period, the intervention will be compared to a self-monitoring without intervention group and a passive control group. Telephone interviews will be conducted at baseline, post-intervention (4 weeks), and 12-week follow-up to assess study outcomes. The primary outcome will be improvement of mental health. Secondary outcomes will include well-being, intentions toward help-seeking and help-seeking behavior, user activation, attitudes toward mental-health services, perceived stigmatization, smartphone app quality, user satisfaction, engagement, and adherence with the intervention. Additionally, data from the user’s daily life as collected during self-monitoring will be used to investigate risk and protective factors of mental health in real-world settings. Therefore, this study will allow us to demonstrate the effectiveness of a smartphone application as a widely accessible and low-cost intervention to improve mental health on a population level. It also allows to identify new assessment approaches in the field of psychiatric epidemiology.

## Introduction

Mental health is broadly defined as “a state of well-being in which an individual realizes his or her own abilities, can cope with the normal stresses of life, can work productively and is able to make a contribution to his or her community” (1). Thus, mental health relates not only to the absence of illness but also to positive functioning in regard to well being and social connectedness, and a sense of control and self-efficacy. Indeed, there are strong links between mental health and work productivity, social inclusion, quality of relationships, and life opportunities in general (2–4). There is also a high comorbidity with other health conditions, where poor mental health acts as a risk factor (5). Over the lifespan, mental-health problems often take an episodic course, where relative symptom-free times alternate with more severe episodes of illness (6). Mental ill-health develops frequently in young adults and tends to become chronic in older age if not adequately treated and managed (7).

Mental ill-health is associated with a high societal burden. The most prevalent mental disorders including major depression, anxiety disorders, insomnia, somatoform disorders, and alcohol and drug dependence are among the leading causes of years lived with disability (8). The estimated cost of all mental disorders taken together amounts to up to €240 billion each year in Europe (9). As a result, these countries have made effective, accessible, and high-quality mental-health care a priority, and have called for increasing action to promote mental health in the population (10, 11).

Despite the existence of effective treatment options, improving the mental health of the population is compromised by a low detection rate and treatment-seeking of persons with mental-health problems. Community mental-health surveys indicate that up to 27% of the adult population is affected by at least one mental disorder each year (12) and up to the age of 50, 3/4 of the population has experienced some kind of mental disorder (13). But even in comprehensive health-care systems with free access to mental-health care, as, e.g., in Germany, only up to one-quarter of all persons with mental disorders receive professional help (14). Manifold barriers to help-seeking exist (15), among others also the stigma of mental disorders and self-stigmatization (16, 17). The high numbers of individuals, unaware of their mental-health problem and who consecutively do not seek treatment, lead to the conclusion that a significant amount of unmet treatment needs exist in the population.

Recently, the WHO suggested the use of mobile health (mHealth) technology to improve access to psychological treatment (18). This is referred to as mHealth. Smartphone technology is now widely available in the population, serving as an attractive, but yet under-used delivery channel for health interventions (19). This technology is suitable of repeated sampling of subjects’ current behaviors and experiences in real time and in natural environments, which is referred to as Ambulatory Assessment (AA), Experience Sampling Method, or Ecological Momentary Assessment (20). It can also be combined with psychological interventions, i.e., Ecological Momentary Interventions (EMI). An EMI is a treatment “provided to people during their everyday lives (i.e., in real time) and settings (i.e., real world)” (21). A particularly promising approach for an EMI is the self-monitoring of mental health, where the user learns to keep track of his or her symptoms and behavior over time. Based on the individuals’ real-time information, tailored feedback can be provided to support and reinforce positive change in mental health, and to counteract negative developments. Mobile self-monitoring could not only support mental health but could also stimulate learning about one’s own mental health, and could lead to improved self-management skills and establishment of healthy attitudes and behaviors.

Self-monitoring offers several advantages. First, conducting repeated measurements of mental-health symptoms reveals insights into the dynamics of psychological processes as they naturally develop and this information can be used improve the prediction of relapses or to track treatment response. Second, by establishing short time intervals between experience and recall, or even assessing the present moment, the problem of recall bias, as in retrospective reports, can be avoided. Third, by capturing the real-world contexts, in which experiences are made or behavior occur, risk and protective factors in the psychosocial environment and their impact on mental health can be more easily identified. Fourth, self-monitoring is executed independently, without clinical supervision, which stimulates an active role of the user and empowers subjects to manage their own health. Fifth, self-monitoring can be combined with automated feedback based on the information provided by the individual, which allows for the development of interventions to support mental health and to integrate these interventions in a daily life routine, when support is mostly needed.

Supportive self-monitoring has been successfully used for a broad range of mental-health problems. It can be a feasible, well-accepted approach among patients with mental-health problems (22), and is associated with improvements in clinical outcomes (23–25). Among young adults in the early stages of depression, self-monitoring increases emotional self-awareness, which is an important first step in a stepped care approach (26). Symptom monitoring as part of a disease management program prolonged symptom-free intervals among patients with recurrent depression (27) and helps to focus on that behavior, which patients can influence themselves (28). Among untreated individuals, a motivating effect to seek health care was found (29). Over 50% of persons with mental disorders in all age groups expressed an interest in daily mental health self-monitoring (22). The available evidence on self-monitoring of mental health is limited as most studies are observational and do not employ control groups. Randomized controlled trial (RCT) are needed to investigate benefits and potential harms.

Whether supportive monitoring can be safely applied in unsupervised settings has not yet been sufficiently documented. Besides technical challenges (e.g., battery problems, availability of internet connection), issues of data security and data privacy are critical. As continuous self-monitoring is likely challenging, especially for person with mental-health symptoms, various factors such as low motivation and energy, the tolerability and desirability from the patients’ perspective need to be examined. It is also unclear which subgroups of patients mostly benefit from this type of intervention. Also, the identification and timely management of crises and risk of harm during self-monitoring must be considered. Several trials have shown negative results, including more sustained symptoms as a result of self-monitoring mental health (30). This indicates that self-monitoring needs in-depth consideration and clarification before it is implemented as a clinical tool in the future.

Before this background, we aim to develop and evaluate to the best of our knowledge the first mHealth intervention for mental health on the basis of supportive self-monitoring in the general population. A field test of mental health self-monitoring in the general population has been conducted previously and serves as the basis of this project (31). Building on a smartphone application for Android devices, the mHealth intervention can be disseminated at low cost, and can achieve broad accessibility in the population. Implementing an indicated prevention approach, we want to focus on adults from the general population with psychological distress, who display lowered productivity in day-to-day activities, but who are not seeking professional help. Examining the intervention across subgroups, subjects with low, moderate and high mental distress will be included, covering all degrees of mental-health problems. As smartphones are increasingly used not only by young people, but across all age groups, the study will include young and middle aged adults aged 18–45. We hypothesize that by using the intervention, participant’s mental health and health-related behaviors will improve.

## Material and Equipment

### Stepwise Procedures

A fully mobile 3-arm RCT will be conducted. The intervention will be compared toward AAs (self-monitoring without support) and a passive control group (no self-monitoring and no support). We hypothesize that using the intervention will improve mental health as compared to the control groups, where we expect no significant changes. The RCT will be registered prospectively as a clinical trial in the German registry for clinical trials (Deutsches Register Klinischer Studien).

#### Target Group

The target group for the mHealth intervention are 18- to 45-year-old Android smartphone users with psychological distress. We differentiate between low, moderate, and high psychological distress, as indicated by the Kessler K6 screening scale. The presence of psychological distress as measured by the K6 indicates elevated psychopathology, functional impairment, and treatment need. This was shown in several population-based studies that used the K6 scale as a screening instrument (32, 33). For high distress, a sensitivity of 0.36, specificity of 0.96, and total classification accuracy of 0.92 has been demonstrated in validation studies against structured diagnostic interviews (33). This indicates that subjects with high distress are likely to fulfill diagnostic criteria for a common mental disorder. Participants with moderate distress likely do not fulfill the diagnostic criteria for a mental disorder, but where shown to experience significant psychopathology, functional impairment, and treatment need as well (32).

The size of the target group in Germany can be roughly estimated with a combination of market data on smartphone sales (34, 35), population census data on age distribution (36), and prevalence rates of psychological distress (32). In 2015, about 63% of the German population owned a smartphone, equaling to about 44 million smartphone owners in Germany (34). The leading smartphone operating system is Android with 79.2% of sold smartphones in 2016 (35). Subtracting persons above 45 or under 18 from the 34 million Android smartphone users, we estimate a total of 12.4 million eligible persons who belong to the target group in Germany (36). From the total target group, 63.5% (7.9 million) is estimated to have low psychological distress, 27.9% (3.4 million) is estimated to have moderate psychological distress, and 8.6% (1.1 million) is estimated to have high psychological distress based on the K6 screening scale (32). These estimates indicate that a broad target group exists in the population that could benefit from the mHealth intervention.

#### Recruitment

We aim for a broad recruitment strategy including online and offline channels to achieve a sample that reflects the target group. Online recruitment on social media is a cost-effective approach, which can recruit large numbers of participants in short time, in particular for e-health studies (37, 38). We will place targeted advertisements on Facebook, the most popular social networking platform with 28 million active users in Germany, and Google, the most popular search engine and, with 660 million daily visitors, one of the most frequented websites. Targeted advertisements (e.g., filtered by age, gender, and smartphone usage) ensures that advertisements will reach the target group. While online recruitment is not necessarily superior to offline recruitment, the combination of both approaches was found to be optimal for achieving a representative sample (39). Therefore, efforts will be undertaken to recruit participants in the community, including placing newspaper advertisements, emails to health professionals and civic organizations, media and press releases at Charité Universitätsmedizin Berlin.

#### Sample Size Calculation

A power analysis was performed to detect a group difference on the primary outcome at post-assessment group. The calculation is based on the assumption that a difference between the supported monitoring group and either AA group or control group within the margin −0.25 < Cohen’s *d* < 0.25 can be neglected. We assume no difference between the two latter groups. Therefore, a between-group difference of *d* = 0.25 should reach statistical significance as an indicator of the general effectiveness of the intervention. The target sample size was computed using Gpower (40) for a repeated-measures analysis of variance for a within-between interaction of time and group (ANOVA). We used a targeted power of 95%, a significance level alpha of 0.05, four assessment waves, a conservative estimate of correlation between measurements (*r* = 65) and variances of the differences between groups (non-sphericity correction epsilon = 0.8). This results in a total *N* = 141. Adding 20% drop-out at T2 and T3, we will include 186 participants (62 per group).

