### Outcomes

Study outcomes are assessed at four time points: screening (T0), baseline (T1), post-assessment (T3) and follow-up (T4). While the screening (T0) relies on self-assessments collected during participant registration on the study website, structured telephone interviews are conducted at T1, T2, and T3 to assess the primary outcome. The telephone interviews will be conducted by the Academic Survey Lab at the University of Hamburg. Trained interviewers who are blinded to the study condition will conduct the interviews, resulting in an independent outcome assessment to avoid confounding with the self-monitoring data. The secondary outcomes will be self-assessed on the smartphone for all three groups.

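### The sample size does not give 95% power for d = 0.25: the planned time × group test has about 25–43% power for that difference

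*Protocol article*

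**What the plan says.** The Sample Size Calculation sets out "to detect a group difference on the primary outcome at post-assessment group". Differences inside ±0.25 SD between supported monitoring and either comparator are treated as negligible. Of the two comparators it says "We assume no difference between the two latter groups". It concludes that "a between-group difference of *d* = 0.25 should reach statistical significance".

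The calculation was made in G*Power for the within-between interaction of a repeated-measures ANOVA: "We used a targeted power of 95%, a significance level alpha of 0.05, four assessment waves", a correlation of 0.65 (printed as 65) and a non-sphericity epsilon of 0.8. It gives N = 141. The last step reads "Adding 20% drop-out at T2 and T3, we will include 186 participants (62 per group".

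Statistical Analysis makes the same interaction the decision rule: the intervention is called effective if time and group interact. Outcomes lists four assessment points including the web screening T0, but says that "structured telephone interviews are conducted at T1, T2, and T3 to assess the primary outcome". That section numbers post-assessment and follow-up in two ways; here T2 is the 4-week assessment and T3 the 12-week assessment.

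**The concern.** The effect is stated as a Cohen's d, but the G*Power routine needs an f for the interaction, and the article prints none. An N as small as 141 is surprising for 95% power at d = 0.25 in three arms: a plain two-arm comparison of post scores would need 416 per arm. This suggests that d was converted to f by a rule that does not fit the design.

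The stake is the trial's headline power claim. If the conversion is wrong, the difference that the plan treats as the edge of relevance is one that the decision test would usually miss, while the article tells readers that it should be detected.

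**Working it through.** **Inputs (Sample Size Calculation; 1:1:1 allocation from the randomization section).** α = 0.05, target power 0.95, k = 3 groups, m = 4 waves, ρ = 0.65, ε = 0.8, d = 0.25 for one group against two equal groups.

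**Step 1: reproduce 141.** For the within-between interaction under the default G*Power effect-size option:

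- λ = f²·N·m·ε/(1−ρ)
- df1 = (k−1)(m−1)ε
- df2 = (N−k)(m−1)ε

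With f = d/2 = 0.125 and N = 141:

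- λ = 0.015625 × 141 × 4 × 0.8 / 0.35 = 20.14
- df1 = 2 × 3 × 0.8 = 4.8
- df2 = 138 × 3 × 0.8 = 331.2

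Power is 0.953. At N = 138 it is 0.948, so 141 is the smallest total divisible by 3 that reaches 95%. Entering f = 0.25 gives 39. The 'as in SPSS' option with f = 0.25 gives 138 and takes no correlation input, although the article says that one was used.

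**Step 2: the f that d = 0.25 implies.** Here f is the standard deviation of the interaction effects in outcome-SD units. With one of three groups shifted, it is d × SD of the group pattern × SD of the time pattern. The group pattern (1, 0, 0) has SD √2/3 = 0.471.

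- Difference at T2 and T3: time pattern (0, 0, 1, 1), SD 0.5; f = 0.25 × 0.471 × 0.5 = 0.059.
- Difference at T2 only: time pattern (0, 0, 1, 0), SD 0.433; f = 0.25 × 0.471 × 0.433 = 0.051.
- Telephone waves T1–T3 only: time pattern (0, 1, 1), SD 0.471; f = 0.25 × 0.471 × 0.471 = 0.056, with m = 3.

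Read backwards on four waves, f = 0.125 corresponds to d = 0.125/(0.471 × 0.5) = 0.53 for the sustained difference, or 0.125/(0.471 × 0.433) = 0.61 for T2 only.

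**Step 3: power at d = 0.25.** For the sustained difference at N = 141, unrounded f = 0.0589 gives λ = 0.0589² × 141 × 4 × 0.8 / 0.35 = 4.48, against the 20.14 of Step 1.

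| Pattern (ε = 0.8) | N = 141 | N = 186, no loss | N for 95% power |
|---|---|---|---|
| Four waves, T2 and T3 | 33% | 43% | 621 |
| Four waves, T2 only | 25% | 32% | 825 |
| Three waves, T1–T3 | 26% | 34% | 831 |

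With ε = 1 the first row rises only to 37% and 49%. A linear build-up over the four waves gives 19% and 24%.

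**Step 4: detectable difference for the same test.** Solving for d with ε = 0.8, over the same three patterns:

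| | N = 141 | N = 186 |
|---|---|---|
| 80% power | 0.42–0.49 | 0.37–0.43 |
| 95% power | 0.53–0.61 | 0.46–0.53 |

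**Step 5: drop-out.** 141/0.80 = 176.25, so 177. 141 × 1.2 = 169.2. With 20% lost at each of T2 and T3, 141/0.64 = 220.3, so 221. None gives 186, which implies a loss of 1 − 141/186 = 24%. Conversely, 186 × 0.80 = 149 completers and 186 × 0.64 = 119.

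**The case against.** **The f is inferred.** The article never prints 0.125. That stands, but the conclusion does not rest on it. Step 3 starts from the stated d, group pattern, correlation and epsilon, and no reading tried gives 95%. The most favourable alternative, a planned contrast of mean (T2, T3) minus mean (T0, T1) against pooled controls, reaches 65% with 47 per group and 77% with 62. It is not the planned test.

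**Four waves agrees with the plan.** Outcomes counts four time points and the per-protocol set requires T0 to T3. A second pre-treatment measure adds baseline information even though it can carry no treatment effect. So counting T0 is not an arithmetic error. What stands is that T0 is a web self-report, while the telephone interviews that assess the primary outcome run from T1 to T3; the fourth wave needs a justification.

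**The drop-out wording is ambiguous.** True, and against a single 20% loss 186 is slightly generous (177 would do). The counts 149 and 119 are completers. The intention-to-treat analysis includes everyone randomized, with multiple imputation, so neither is the primary analysis set, although imputation does not restore the lost information in full.

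**Two stronger readings fail.** A reader might infer that the trial could easily miss an effect twice as large. The figures do not support this: at d = 0.50 and N = 141 the interaction test has 92% power (sustained) or 82% (T2 only, or three waves). Only the linear build-up, at 67%, is clearly lower. A reader might also infer that a null result will be taken to exclude d = 0.25. The article calls smaller differences negligible, but its only stated rule is that an interaction means effectiveness; it draws no equivalence conclusion from non-significance.

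**Conclusion.** The power statement is wrong as written. For d = 0.25 in one of three groups, the planned time × group test has about 25–33% power at N = 141 and 32–43% if all 186 are analysed, not 95%. This assumes equal correlations of 0.65, ε = 0.8, no difference before randomization, and a difference that is present in full at T2 and either persists to T3 or does not. The three-wave version lies inside those ranges. The gap matches a d/2 conversion applied to an interaction; that cause is an inference from an exact match, whereas the power shortfall is not. The unexplained step from 141 to 186 is real but secondary.

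This does not show that 186 is an unreasonable size. It shows that 186 suits differences of roughly 0.37–0.43 SD at 80% power, before any loss, and not the 0.25 SD that the plan names.

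**What to change.** Keep 186 and rewrite the paragraph for the planned time × group interaction test:

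- Print the f used and how it follows from the assumed group means over time.
- State the detectable difference: at 80% power about d = 0.42–0.49 at N = 141 and 0.37–0.43 at N = 186; at 95% power about 0.53–0.61 and 0.46–0.53.
- State that power at d = 0.25 is about 25–43%, and remove the sentence that this difference should reach significance.
- Base the calculation on the waves at which the K6 is taken by telephone (T1–T3), or justify counting T0.
- Give one drop-out rule and the completers it implies: 149 if 20% overall, 119 if 20% at each of T2 and T3.

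The cost is one rewritten paragraph and a less favourable stated power. No participants are added, and the article reports the trial as still in preparation.

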#### Inclusion Criteria, Informed Consent, and Randomization

The inclusion criteria are age between 18 and 45 years and ownership of an Android smartphone (Android Version 4.0 or higher) with an active internet connection. Exclusion criteria are the presence of suicidal thoughts as measured by one item on the presence of suicidal thoughts, and failure to provide informed consent.

Upon registration, participants will be informed about the requirements and procedure of study on the study website. Additionally, an information booklet with details on the study procedure will be available for download. Informed consent will be obtained of each participant with a written signature when first using the smartphone application. To randomize participants to study conditions, a computerized block randomization procedure will be used (Allocation ratio 1:1:1, block size 10). The researcher preparing the randomization procedure will have no information about participants and will not participate in the recruitment, enrollment of participants, or assignment of participants to study groups.

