### Statistical Analysis

Before analysis, data will be prepared and cleaned according to the guidance in Ref. (99). Data will then be analyzed according to the recommendations in the CONSORT statement for evaluation of e-health interventions, as well as the mHealth evidence reporting and assessment checklist from the WHO mHealth Technical Evidence Review Group (100, 101). Intention-to-treat analysis (ITT) and additional per-protocol analysis (PP) will be performed, the former including the data of all participants randomized and the latter using only the subset of participants who complete all assessments (T0, T1, T2, T3).

Multilevel models are an appropriate data-analytic strategy for smartphone data, involving daily measurements, resulting in repeated observations nested within individuals (102). These models are well suited to test the general effectiveness of supported monitoring among smartphone users, but also its differential effectiveness and its conditional effectiveness. Models include analysis of both within-person and between-person variance. Missing data will be replaced using Markov Chain Monte Carlo multiple imputation, which is considered to produce more precise estimates of the true intervention in the ITT analysis compared other imputation methods, i.e., last observation carried forward (103).

*General effectiveness*: to test for changes in the outcome variable from before to after the intervention period, repeated-measures analysis of variance (RM-ANOVA) will be conducted for each intervention outcome (104). In the RM-ANOVA, the within-person effect of time is used as an index of general intervention effectiveness. For the analysis of between-person variance, the model can be extended to multivariate analysis of variance (MANOVA). In this case, a between-subjects factor for group membership is added (Supported monitoring group vs. AA group vs. control group). If there is an interaction between the time factor and the group factor, we will conclude that the intervention was effective.

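### The enrolment target of 186 does not follow from N = 141 and the printed 20% drop-out; the rate and the number need to be reconciled

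*Protocol article*

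**What the plan says.** The Sample Size Calculation section describes a G*Power calculation "for a repeated-measures analysis of variance for a within-between interaction of time and group (ANOVA". Its inputs are an effect for which "a between-group difference of *d* = 0.25 should reach statistical significance", then "We used a targeted power of 95%, a significance level alpha of 0.05, four assessment waves", a "correlation between measurements (*r* = 65"), which can only mean 0.65, and a "non-sphericity correction epsilon = 0.8". The result is a total of 141. The next sentence moves to the enrolment target: "Adding 20% drop-out at T2 and T3, we will include 186 participants (62 per group"). No inflation formula is shown, and the text does not say whether 20% is the total loss by the last wave or the loss at each of the two waves.

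The Statistical Analysis section plans an intention-to-treat analysis of everyone randomized, with multiple imputation of missing data. It adds a per-protocol analysis, "the latter using only the subset of participants who complete all assessments (T0, T1, T2, T3").

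**The concern.** The step from 141 to 186 is meant to protect the stated 95% power against drop-out. It is printed as a consequence of 20%, but the arithmetic does not give 186. A reader therefore cannot tell which loss the trial was sized to absorb: 20% in total, 24%, or 36% (20% lost twice, 1 − 0.8 × 0.8).

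This matters in two ways. First, a headline design figure cannot be reproduced from its stated inputs. Second, the sentence names two waves. If 20% is expected to be lost at each, 186 leaves fewer people with all assessments than the 141 the calculation asked for. The plan's Limitations section itself names loss to follow-up as a threat to power, so the retention the study can tolerate should be readable from the document.

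**Working it through.** **Inputs.** From Sample Size Calculation: d = 0.25, power 0.95, alpha 0.05, m = 4 waves, r read as 0.65, epsilon = 0.8, N = 141, drop-out 20%, enrolment 186. From the randomization section: three groups ("Allocation ratio 1:1:1, block size 10"), so k = 3. Two readings are mine. I take f = d/2 = 0.125, because the conversion is not printed. I take T2 as the 4-week and T3 as the 12-week assessment.

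**Step 1. Reproduce 141.** For the within-between interaction:

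- λ = f² × N × m × ε / (1 − r)
- df1 = (k − 1)(m − 1)ε
- df2 = (N − k)(m − 1)ε

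At N = 141:

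- λ = 0.015625 × 141 × 4 × 0.8 / 0.35 = 20.14
- df1 = 2 × 3 × 0.8 = 4.8
- df2 = 138 × 3 × 0.8 = 331.2
- power from the noncentral F = 0.953

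Stepping up in threes to keep the groups equal, 141 is the first N that reaches 0.95. The base figure is reproduced, which supports the reading f = 0.125 and confines the problem to the inflation step.

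**Step 2. Inflate 141 by the printed 20%.**

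| Reading of 20% | Dividing by the fraction retained | Multiplying up |
|---|---|---|
| Total loss | 141 / 0.8 = 176.25, so 177 | 141 × 1.2 = 169.2, so 170 |
| At each of two waves, compounded | 141 / 0.64 = 220.3, so 221 | 141 × 1.44 = 203.04, so 203 to 204 |
| 20% of the original sample, twice | 141 / 0.6 = 235 | 141 × 1.4 = 197.4 |

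None gives 186. Rounding to equal groups does not explain the gap, because 177 is already 3 × 59.

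**Step 3. What 141 and 186 imply.**

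- Total loss: 1 − 141/186 = 24.2%.
- Equal loss at each of two waves: 1 − √(141/186) = 12.9%.

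Neither rate is printed. The number can be reached with a second, unprinted rate, for example 141 × 1.2 × 1.1 = 186.1 or 141 / (0.8 × 0.95) = 185.5. A different rate may therefore have been used at one wave and not reported.

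**Step 4. What 186 leaves.**

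- 20% in total: 186 × 0.8 = 148.8, about 149, which is above 141. At N = 149, λ = 0.015625 × 149 × 3.2 / 0.35 = 21.29, df2 = 350.4, and power is about 0.963.
- 20% at each wave: 149 at T2, then 186 × 0.8 × 0.8 = 119.0 with all assessments, which is 22 below 141. At N = 119, λ = 0.015625 × 119 × 3.2 / 0.35 = 17.0, df2 = 278.4, and power = 0.908.

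**The case against.** The best defence is that the phrase need not mean 20% at each wave. The text says neither that the loss is per wave nor that it compounds. If 20% is the overall loss, 186 is more than enough: 149 remain against 141 needed. That stands, and it is why the shortfall to 119 can only be conditional. It does not rescue the sentence, because a total loss of 20% calls for 177, not 186.

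A reader might go further and conclude that the trial as a whole is under-powered, with the main analysis resting on 119 people. The documents do not support this. The intention-to-treat analysis keeps all randomized participants and imputes missing values. Only the additional per-protocol set requires every assessment. Someone lost only at T3 still contributes the earlier waves, and at a correlation of 0.65 these carry information about the missing value. Imputation does not fully restore what is lost, but 0.908 is a completer figure and is pessimistic for the intention-to-treat analysis. The section also opens by naming the post-assessment difference as its target, and 149 remain at that point even on the harsher reading. Against that, the calculation uses four waves, so the powered test also draws on follow-up.

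A reader might also note that the telephone interviews for the primary outcome cover only three waves, and compute 84.8% power at 119. That mixes in a separate change. With three waves, power is already 0.908 at 141 before any drop-out, so most of that fall is not due to attrition.

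Finally, the study-flow figure is not visible in the text at hand and may show expected numbers. The printed sentence would still need correcting.

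**Conclusion.** The sentence is wrong as written: 186 is not what 141 and 20% yield on any standard reading. This rests on arithmetic alone.

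The consequence depends on what 20% means:

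- **Total loss:** the sample is adequate (about 149 remaining, power about 96%), and the fault is only in the derivation.
- **Loss at each wave:** the complete-assessment set is expected to hold 119 people and has about 91% power instead of 95%. The chance of missing the target effect in that set rises from about 5% to about 9%. The intention-to-treat analysis would lose less.

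The power figures assume f = 0.125, r = 0.65 and the plan's own four waves. The effect on power is moderate at worst and does not put the enrolment target itself in doubt. The correction is worth making because the figure is central and the change is cheap.

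**What to change.** Keep 186. In the Sample Size Calculation section, state the drop-out assumed at T2 and at T3, say whether it is cumulative, and rewrite the sentence so that the rate and 186 agree. As a guide, 186 tolerates at most about 24% cumulative loss (about 13% per wave) before the number with all assessments falls below 141. That is a limit worked back from the two printed numbers. It should be given as the assumption only if it is what was assumed.

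If 20% at each wave is meant, state that 149 are expected at T2 and 119 at T3, and restate the power for the complete-assessment set as about 91%.

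The cost is one or two sentences. No participants are added and the design does not change. The only downside is a slightly less favourable stated power or tolerated drop-out.
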